**Methods:**

This randomised and controlled trial will examine whether PA is decreased by access to electronic games and whether any effect is dependent on the type of game input or the child's characteristics. Children aged 10–12 years (N = 72, 36 females) will be recruited and randomised to a balanced ordering of 'no electronic games', 'traditional' electronic games and 'active' electronic games. Each child will participate in each condition for 8 weeks, and be assessed prior to participation and at the end of each condition. The primary outcome is PA, assessed by Actical accelerometers worn for 7 days on the wrist and hip. Energy expenditure will be assessed by the doubly labelled water technique and motor coordination, adiposity, self-confidence, attitudes to technology and PA and leisure activities will also be assessed. A sample of 72 will provide a power of > 0.9 for detecting a 15 mins difference in PA (sd = 30 mins).

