### Participants

36 boys and 36 girls (10–12 years of age) will be progressively recruited by mass media, community newsletters and local school notices. This age group has been selected as they are able to provide detailed information in diary and questionnaires, have a high use of electronic games and are developing activity patterns pre-puberty which may track into adulthood. Recruitment will be staggered over three years and targeted to enable participation of equal numbers of males and females, and children representative of a spread of socio-economic status, electronic game experience and motor competence Volunteers will be screened to ensure they are willing to participate after being informed of the full study responsibilities and meet the inclusion and exclusion criteria. Inclusion criteria are: aged 10–12 years at start of study and able to use electronic games on most days. Children will be excluded if they have a diagnosed disorder likely to impact their study participation, movement or electronic game use (other than developmental coordination disorder), live in a shared care arrangement where the child spends a significant amount of time in different houses and is unable to maintain game access condition, or live remote to the University campus. In 2009, 12 boys and 12 girls will be tested, with equal numbers tested 2010, and 2011.

For power calculations, daily moderate/vigorous PAL was estimated at 115+30 mins with a minimum effect size of 15 mins considered important based on effects in prior studies by us and others [51]. If the variation in the PA level between repeated time points in each individual is normally distributed with standard deviation 30 mins, and the true effect of game condition is 15 mins, a study with 72 subjects will reject the null hypothesis that this response difference is zero with probability (power) 0.986. The Type I error probability associated with this test of this null hypothesis is 0.05. If the Type I error is lowered to 0.01 to account for 'repeated' contrasts between conditions, the power is 0.943 [52]. We [51] have had a compliance rate of 95% for DLW data collection and 92% for accelerometry, and both measures have been widely used in studies of 50 to 100 children [53,9]. We have allowed for 10% attrition in data.

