### Outcome measures

#### Physical activity

Time spent in moderate to vigorous intensity PA, as well as total movement, will be assessed over 7 days using two Actical accelerometers worn on the wrist and the hip. The MiniMitter Actical is the most widely used and validated accelerometer in studies of children and adolescents [54,9]. Seven days of accelerometer measurement are recommended for the purposes of acceptable measurement of moderate to vigorous PA [9]. Total weekly PA as well as weekend PA and after school weekday PA will be assessed.

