### Analysis

To examine hypotheses 1 (that PA and energy expenditure will be reduced when children have access to traditional electronic games) and 2 (that PA and energy expenditure will be greater with new active electronic games, but still less than no games) a 4 (baseline and 3 game conditions) × 2 (sexes) repeated measures ANCOVA analysis with pre-specified contrasts will be conducted for each PA and energy expenditure variable. Prior game experience will be used as a covariate. A critical alpha level of 0.01 will be used to balance type 1 and type 2 errors.

To assess hypothesis 3 (that there will be a stronger effect on children with poor coordination skills, high adiposity, poor social confidence, more positive attitudes to technology and less positive attitudes to PA), separate multiple linear regression analyses for both traditional sedentary electronic and new active electronic games will examine the importance of individual characteristics on activity levels (total minutes of overall moderate/vigorous PA). Sex and amount of moderate/vigorous PA at the end of the no game period will be included as baseline covariates for the assessment of the independent effect on PA of; motor competence, adiposity, perceived athletic competence and attitudes to technology. To assess if individual characteristics may impact differently upon the relationship between PA and traditional sedentary electronic versus PA and new active electronic games, beta coefficients and associated 95% confidence intervals, and proportions of total variance explained by these variables, will be compared between the two models.

To assess hypothesis 4 (that all electronic games will displace active non-electronic leisure activities) the impact of the three study conditions on time spent in four outside school activities (reading, watching TV, using computers, playing sports and non-organised physical activity) will be examined using a 3 (no electronic games, traditional electronic games, active electronic games) ×2 (sex) repeated measures MANOVA with weekly minutes in each activity as the dependent variables.

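### The primary outcome, physical activity, is not reduced to one variable, and the 0.01 level applied to every activity variable is justified only for contrasts between conditions

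*Protocol article*

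**What the plan says.** The abstract (Methods) states: "The primary outcome is PA, assessed by Actical accelerometers worn for 7 days on the wrist and hip". It names no metric, no single site and no time window.

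Outcome measures, Physical activity, gives the components. On metric and device: "Time spent in moderate to vigorous intensity PA, as well as total movement, will be assessed over 7 days using two Actical accelerometers", one on the wrist and one on the hip. On time window: "Total weekly PA as well as weekend PA and after school weekday PA will be assessed".

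The Analysis section, for hypotheses 1 and 2, plans an ANCOVA for repeated measures, with contrasts fixed in advance, "for each PA and energy expenditure variable". Hypothesis 2 is that "PA and energy expenditure will be greater with new active electronic games, but still less than no games". The level is set once for all of these analyses: "A critical alpha level of 0.01 will be used to balance type 1 and type 2 errors".

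The only other reason for that level is in Participants, in the power paragraph. The sentence opening "If the Type I error is lowered to 0.01 to account for" goes on to name repeated contrasts between conditions. That calculation concerns a single variable, daily moderate/vigorous minutes.

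**The concern.** A primary outcome that is a label for several measured variables, each tested at the same level, leaves two questions open.

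- **Error.** A level chosen to allow for several contrasts on one variable does not allow for several variables. Each additional PA variable is another opportunity for a false positive on the primary outcome.
- **Interpretation.** Suppose the hip shows less activity with traditional games and the wrist does not, or the weekend result is significant and the weekly one is not. The plan does not say which result answers hypothesis 1 or 2, and a favourable one could be chosen after the data are seen.

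This is more than detail left to an analysis plan. The article itself states the primary outcome, the testing rule and the level, and the three do not fit together.

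**Working it through.** **Step 1: the plan's own power figures.** Inputs from Participants: n = 72, difference 15 min, SD 30 min (read as the SD of the within-child difference). For a two-sided paired t-test with 71 df, the noncentrality is 15 / (30/√72) = 4.243.

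| Level | Computed power | Stated power |
|---|---|---|
| 0.05 | 0.987 | 0.986 |
| 0.01 | 0.941 | 0.943 |

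Both reproduce. They describe one contrast on one variable.

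**Step 2: how many variables and contrasts.** The article gives neither count.
- Crossing everything listed: 2 metrics × 2 sites × 3 windows = 12 PA variables.
- Hypotheses 1 and 2 imply three pairwise contrasts: none versus traditional, traditional versus active, none versus active.
- Full crossing therefore gives 12 × 3 = 36 tests.

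Both counts are inferences.

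**Step 3: one variable.** Three pairwise contrasts among three conditions, each two-sided at 0.01 under the global null, share data. Simulation gives a chance of 2.7% of at least one rejection (Bonferroni bound 3 × 0.01 = 3%). Counting only the hypothesised directions (none > traditional, active > traditional, none > active) gives 1.4%.

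**Step 4: several variables.** Method: simulated null trials (400,000 draws), equally correlated variables, three ungated contrasts per variable at two-sided 0.01. The article gives no correlations, so they are varied. Simulation error is about 0.1 percentage point.

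| Correlation | 12 variables, two-sided | 12 variables, hypothesised directions | 2 variables, two-sided |
|---|---|---|---|
| 0 | 28% | 15.6% | 5.4% |
| 0.5 | 20% | 10.9% | 5.0% |
| 0.7 | 15% | 8.0% | 4.7% |
| 0.8 | 12% | 6.3% | 4.4% |
| 0.9 | 8.4% | 4.5% | 3.9% |
| 0.95 | 6.4% | 3.3% | 3.6% |

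Check at correlation 0: 1 − (1 − 0.027)^12 = 28%, and 1 − (1 − 0.0141)^12 = 15.7%.

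The two-variable column is the case where metric and window are taken as settled and only the site is open.

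**Step 5: sensitivity (two-sided).**
- Four variables: 10.4% at correlation 0, 5.5% at 0.9.
- Six variables: 15.3% at correlation 0, 6.5% at 0.9.
- Twelve variables, with contrasts read only after a 0.01 omnibus test (a gate that the article does not state): 11.4% at correlation 0, 3.4% at 0.9.

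**Step 6: power of the remedy.** With 10% attrition, 72 × 0.9 ≈ 65 children. The same paired t-test gives 0.911 at 0.01 and 0.978 at 0.05.

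**The case against.** The strongest reply is that a lead variable is already implied. The sample size uses daily moderate/vigorous minutes, and the hypothesis 3 analysis uses total minutes of overall moderate/vigorous activity. On that reading only the site is open, and two variables give at most about 5.4%, close to a conventional 5%. The reading is fair and shows what the sponsor probably had in mind. But nothing declares that variable primary, the Analysis section tests every PA variable on equal terms, and even this reading does not choose between wrist and hip.

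The large percentages are also fragile. The top of the range assumes independent variables, which is implausible when the weekly total contains the weekend and after-school periods and both metrics come from the same devices. Two-sided counting includes results opposite to the hypotheses, and dropping those roughly halves the figure. An omnibus gate would lower it further. All of this stands, and is why the figures are given as an illustration over a range.

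Three stronger readings are tempting, and the article does not support them:
- **The plan specifies twelve primary variables and 36 tests.** It lists the components but never says that they are fully crossed, and it gives no number of contrasts.
- **The plan misses an error rate that it set out to hold across variables.** It states no such target. It gives a per-test 0.01 and two reasons for it.
- **Wrist and hip can be expected to disagree because active games are mostly arm movement.** The Background describes the camera game as sensing arm, leg and trunk position, and the active condition also includes a stepping mat. Disagreement is possible, but the article does not predict it.

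A condensed article may leave a detailed testing hierarchy to an analysis plan. That excuses the absence of a full list of contrasts. It does not excuse a stated rule that tests every component of the primary outcome at a level justified for one.

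**Conclusion.** The point holds in a limited form. The primary outcome is not reduced to one variable, the 0.01 level is explained only for contrasts within a variable, and nothing decides which PA result answers hypotheses 1 and 2. These facts are in the text and need no simulation.

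The size is uncertain because it rests on an inferred number of variables and contrasts, assumed equal correlations and no gate. For the full crossing, error is about two to ten times that for a single variable. If only the site is open, the inflation is modest, and the lack of a deciding rule is the larger problem. The power figures themselves are not in error.

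**What to change.** In the abstract, Outcome measures (Physical activity) and Analysis:

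1. Declare one primary variable: daily moderate/vigorous minutes over the full 7 days, as used for the sample size, from one accelerometer site that is chosen and stated before analysis. The article gives no ground for preferring wrist or hip, so the sponsor should choose and give the reason.
2. List its contrasts. Keep them at 0.01, which holds the error over three contrasts at 2.7%, or test them in a pre-stated fixed order at 0.05. Either is acceptable.
3. Label the other site, total movement, weekend, after-school, total energy expenditure and PAL-ratio results as secondary, either Holm-adjusted or reported as descriptive estimates.

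**Cost.** Only wording changes. The secondary variables lose confirmatory status. Power for the primary contrast is not reduced: with 65 children it stays at 0.91 at 0.01, and is 0.98 for the first contrast in a fixed order at 0.05. Keeping all 36 tests of a full crossing confirmatory would instead need 0.05/36 = 0.0014 per test under Bonferroni.

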**Figure 1 F1:**
[figure not shown]
**Mean (SE) accelerometer assessed weekly energy expenditure during three electronic game access conditions**.

The second reason why current evidence may be limited is that epidemiological studies have often used only age, sex and socioeconomic status as covariates in their models of the relationship between electronic game playing and PA when other variables may be equally or more influential.

Psychosocial variables are known to influence PA levels in children (e.g. perceived athletic competence [45]) and our research has found an impact on use of technology (e.g. children's experience of flow). The most widely used model of technology use (Davis' Technology Acceptance Model [46]) predicts that positive perceptions of technology increases the use of technology and this has been shown to be the case with computer use but has not been investigated with electronic game use. Biological variables are also known to influence PA by children. Children with poorer motor competence engage less in PA than other children [47] and overweight children spend more time with SBM [32]. Our pilot study data suggests the impact of electronic game access varied considerably between children. Therefore a further reason why current evidence is weak may be that sufficient appropriate covariates have not been added to epidemiological models. This project will explore a range of psychosocial and biological variables to inform future epidemiological studies.

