## Methods/Design

### Design and Aims

This study will use a randomised and controlled trial to assess the impact of electronic game use on PA in children by:

1) comparing PA and energy expenditure where children have either no electronic games or access to traditional electronic games. We hypothesise that PA and energy expenditure will be reduced when children have access to traditional electronic games.

2) comparing PA and energy expenditure where children have access to either traditional electronic games, new active electronic games and no electronic games. We hypothesise that PA and energy expenditure will be greater with new active electronic games, but still less than no games.

3) examining responses of different children to explore whether the impact of access to electronic games is greater in some children. We hypothesise a stronger effect on children with poor coordination skills, high adiposity, poor social confidence, more positive attitudes to technology and less positive attitudes to PA.

4) examining displacement of sedentary and active leisure activities by electronic games. We hypothesise that all electronic games will displace active non-electronic leisure activities.

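### Hypothesis 3 regressions adjust for one noisy week of no-game PA, so a trait that merely tracks PA level can look like a moderator of the game effect

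*Protocol article*

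**What the plan says.** Under Design and Aims, the third aim is a moderation question: "We hypothesise a stronger effect on children with poor coordination skills, high adiposity, poor social confidence", followed by more positive attitudes to technology and less positive attitudes to PA.

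The Analysis section commits to a model for it: "separate multiple linear regression analyses for both traditional sedentary electronic and new active electronic games will examine the importance of individual characteristics on activity levels", with total minutes of moderate/vigorous PA as the outcome. Then: "Sex and amount of moderate/vigorous PA at the end of the no game period will be included as baseline covariates". Four characteristics are examined in this way, each for its own contribution: adiposity, motor competence, attitudes to technology and perceived athletic competence. To contrast the two game types, "beta coefficients and associated 95% confidence intervals, and proportions of total variance explained by these variables, will be compared between the two models".

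Two other statements matter. The Background says "Children with poorer motor competence engage less in PA than other children", names perceived athletic competence as an influence on PA, and links low childhood PA with obesity. Under Outcome measures, PA in each condition comes from one 7-day accelerometer recording.

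**The concern.** The quantity of interest is how the change in PA between no games and games varies with a trait. The planned model asks something else: among children with the same measured no-game PA, do those with different trait values differ in game-condition PA? The two questions coincide only if no-game PA is measured without error or the trait is unrelated to PA.

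Take two children with the same no-game score in one week, one well and one poorly coordinated. If poorly coordinated children are usually less active, the second child was more likely having an unusually active week. In the next condition that child tends to fall back towards a lower usual level, and the model reads the fall as a larger loss of PA due to games. A trait that only predicts how active a child is would then be reported as a characteristic that makes games more harmful. The Background says these results are meant to inform which covariates later epidemiological models should carry.

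**Working it through.** **Inputs from the protocol (Participants).** "daily moderate/vigorous PAL was estimated at 115+30 mins with a minimum effect size of 15 mins considered important", read as mean 115, SD 30; "variation in the PA level between repeated time points in each individual is normally distributed with standard deviation 30 mins"; N = 72; stated power 0.986 at alpha 0.05 and 0.943 at alpha 0.01. The protocol gives no correlation between any trait and PA, so that is an assumption (ρ) shown over a range.

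**Step 1: which SD is the 30 min?** A two-sided paired t-test (71 df) for a 15 min effect gives:
- 30 min as the SD of the within-child difference: power 0.987 and 0.941, matching the stated figures.
- 30 min as the per-occasion SD (difference SD 30 × √2 = 42.4): 0.841 and 0.638, which do not match.

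So 30 min is the SD of the difference.

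**Step 2: implied correlation between conditions.** Var(difference) = 2 × 900 × (1 − R) = 900, so R = 0.5. R equals the reliability of no-game PA only if all within-child variation is noise; Step 5 relaxes this.

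**Step 3: expected trait coefficient with no moderation.** Let usual PA be T = bX + u, with X a standardised trait and b = 30ρ. Let no-game PA be T + e0 and game PA be T − 15 + e1. Regressing game PA on X and no-game PA gives an expected coefficient on X of

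b × (1 − λ), where λ = var(u) / (var(u) + var(e)) = (R − ρ²) / (1 − ρ²).

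For R = 0.5 and ρ = 0.3: b = 9, var(u) = 450 − 81 = 369, var(e) = 450, λ = 369/819 = 0.451, coefficient = 9 × 0.549 = 4.95 min per trait SD. The true moderation is zero. For ρ = 0.2 and 0.4 the same formula gives 3.1 and 7.1 min.

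**Step 4: false-positive rate at nominal 5%.** Simulation, n = 72, sex in the model, one trait at a time, no moderation:

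| Between-condition correlation | ρ = 0.2 | ρ = 0.3 | ρ = 0.4 |
|---|---|---|---|
| 0.5 | 16% | 32% | 56% |
| 0.7 | 11% | 19% | 34% |
| 0.9 | 7% | 8% | 13% |

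With 65 children (10% attrition) and R = 0.5 the rates are 15%, 29% and 51%. In the same simulations, regressing the within-child difference on trait and sex gave coefficients within about 0.1 min of zero and false-positive rates of 4.5% to 5.7%.

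**Step 5: two settings that shrink the figures.**
- *Four traits together*, as the plan intends (assumed inter-trait correlation 0.3, R = 0.5). The partial slope is 30ρ/(1 + 3 × 0.3), which for ρ = 0.3 is 9/1.9 = 4.74. The traits jointly explain 4 × 0.3 × 0.3/1.9 = 0.189 of the PA variance. Hence λ = (0.5 − 0.189)/(1 − 0.189) = 0.383, and the coefficient is 4.74 × 0.617 = 2.9 min. Simulated per-trait rates for ρ = 0.2, 0.3, 0.4 are about 7–9%, 14% and 31%. The chance that at least one of the four is flagged is about 28%, 46% and 79%, against about 18% under the difference model.
- *Genuine variation in response* (assumed SD 20 min, unrelated to the trait). Then 900 = 400 + 2var(e), so var(e) = 250 and the reliability of no-game PA is 650/900 = 0.72. Single-trait rates are about 7%, 11% and 18%.

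**Step 6: direction.** The bias carries the sign of the trait–PA association: positive for motor competence and perceived athletic competence, negative for adiposity. In each case the less active group appears to lose more PA, as hypothesised. (The Analysis lists athletic competence where the aim names social confidence; I take the predicted direction to be the same.)

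**The case against.** The best case for the plan has four parts.

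First, the larger rates come from one trait at a time and from treating all within-child variation as error. The plan enters several traits, and the Background reports that the pilot response varied considerably between children. Seven days is also the recommended recording length. This stands as a limit on size: under those conditions the per-trait rates are the lower ones in Step 5. It does not bring the expected coefficient to zero.

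Second, a reader might infer that any trait correlated with PA will emerge as a false moderator in the predicted direction. The documents do not support that. They give no trait–PA correlation at all, and no direction for attitudes to technology; the Background notes that some children with high screen use are also more active. At low correlations or high reliability the excess over 5% is small.

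Third, a reader might infer that the traditional-versus-active comparison is biased in the same way. It is not: both models carry about the same bias, and the simulated difference between their coefficients was about zero. What remains is that separate intervals from the same children, adjusted for the same no-game score, do not test that difference. The article announces no decision rule, and its form may be left to a fuller plan.

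Fourth, the aim is exploratory. That bears on severity, not on whether the model answers the question.

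**Conclusion.** The concern holds for the trait coefficients within each of the two regressions. With no moderation, each is expected to equal (1 − partial reliability of no-game PA) × (partial slope of the trait on usual PA), which is zero only if reliability is perfect or the trait is unrelated to PA. For the three traits whose PA link the protocol itself states, the error favours the hypothesis.

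The size is uncertain. Across the settings in Steps 4 and 5, with trait correlations of 0.2 to 0.4, the false-positive rate at nominal 5% runs from about 7% to 56%. The upper end needs one trait at a time and a between-condition correlation of 0.5, which follows from the power inputs only if all within-child variation is noise.

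This should be fixed, but it does not threaten the trial's main result: the condition comparisons under hypotheses 1 and 2 use a separate within-child analysis.

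**What to change.** Replace the two regressions with a direct test of moderation, in either of two ways:
- one mixed model over the three conditions, with a random child effect, period, sex, the characteristic, and condition by characteristic; or
- regressions of the within-child differences (traditional − none, and active − none) on characteristics measured at baseline and on sex, without no-game PA as a covariate.

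If adjustment for usual activity is wanted, the pre-trial baseline week may be added, but only when the outcome is the within-child difference. Swapping it for the no-game score while keeping game-condition PA as the outcome does not remove the bias.

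As a secondary change, compare game types by regressing (active − traditional) on the characteristic.

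The cost is analysis wording only, with no new data. Intervals widen slightly: at a correlation of 0.5 the residual SD is about 30 min for the difference, against 30 × √(1 − 0.25) = 26 min for the planned model.

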## Background

Nationally and internationally, promoting physical activity (PA) has become a major health priority. In the USA, Healthy 2010 has PA ranked as a leading health indicator [1] and the Department of Health in the UK have recently launched their "At least five a week" PA call for action [2]. In Australia, the Strategic Inter-Government forum on Physical Activity and Health was established in 1999 as the collaborative body to coordinate a national approach in supporting health-promoting PA in Australia. The resultant "Be Active Australia" framework was endorsed in 2005. Increasing PA is now a priority issue of state governments across Australia (eg  and ) with Queensland even calling 2008 "The year of Physical Activity" .

PA in adulthood is an important inverse risk factor for the major causes of mortality and morbidity including heart disease, stroke, cancer, musculoskeletal disorders, depression, obesity and diabetes [3]. Insufficient PA contributes a major international health burden [4-6] with Australian direct health care costs estimated at more than $400 million p.a. [7]. In Australia, insufficient PA has been estimated to account for 8,000 deaths per year and is the 4th leading cause of premature death, after obesity, tobacco and hypertension [8].

Whilst the data are inconclusive as to whether PA levels in children track through to adulthood [9], there is evidence to suggest that inactivity tracks [10]. Furthermore, lower levels of PA in childhood have been linked in the short-term with increased levels of obesity, poorer skeletal health [11], and poorer psychosocial well-being [12]. Whilst there is an absence of definitive data providing a causal link between PA and health, Biddle et al. conclude that the evidence suggests that PA in childhood has beneficial effects on cardiovascular disease, obesity, psychosocial outcomes, type II diabetes and osteoporosis [13].

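### Hypothesis 3 is about who loses more activity with games, but the planned regression adjusts activity level for one no-games week, so traits that track habitual activity get a biased coefficient

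*Protocol article*

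**What the plan says.** The third aim (Design and Aims) is about effect modification: "We hypothesise a stronger effect on children with poor coordination skills, high adiposity, poor social confidence", with attitudes to technology and to PA completing the list. The effect in question is the change in a child's activity between having no games and having games.

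The Analysis section assigns this to "separate multiple linear regression analyses for both traditional sedentary electronic and new active electronic games". These models "will examine the importance of individual characteristics on activity levels (total minutes of overall moderate/vigorous PA"), so the outcome is the level of MVPA in a game condition. For adjustment: "Sex and amount of moderate/vigorous PA at the end of the no game period will be included as baseline covariates". The traits entered are motor competence, adiposity, perceived athletic competence and attitudes to technology. Coefficients, 95% confidence intervals and variance explained are then compared between the two game types. No within-child difference and no trait-by-condition term is specified.

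Activity is recorded once per condition, over 7 days at its end (Physical activity; Trial flow). The Background says that the traits track activity. On motor competence: "Children with poorer motor competence engage less in PA than other children". On adiposity: "lower levels of PA in childhood have been linked in the short-term with increased levels of obesity". It also names perceived athletic competence as an influence on children's PA.

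**The concern.** A single week measures a child's habitual activity with error. Conditioning on it removes only part of the habitual level, and a trait correlated with that level picks up the rest. Take two children with the same observed no-games MVPA, one well and one poorly coordinated. The poorly coordinated child's no-games week was, on average, high for that child, so the games week will tend to be lower even if games take the same number of minutes from both. The model shows this as a trait coefficient, which would be read as a stronger effect of games in poorly coordinated children. That is the direction hypothesised. For adiposity the sign reverses and the reading is the same.

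The traits are observed, not randomised, so the usual argument for covariate adjustment in a randomised comparison does not carry over. Nor is the no-games week a true baseline. With all six orders balanced (Procedure), no games precedes a given game condition in 3 of 6 orders, so for 36 of 72 children the covariate is measured after the outcome.

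At stake is whether hypothesis 3 could appear supported when no trait modifies the effect, or whether real modification in the opposite direction could be reduced.

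**Working it through.** **Inputs from Participants.** 72 children; effect 15 min; within-child SD 30 min; 10% attrition (72 × 0.9 ≈ 65). The between-child figure is given as "daily moderate/vigorous PAL was estimated at 115+30 mins", with 30 read here as the SD. **Assumed, because the documents do not give it:** correlation w between a trait and weekly MVPA of 0.2, 0.3 or 0.4, with the trait scored so that higher goes with more activity.

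**Step 1: the plan's power.** A paired t-test with SD of the difference 30 has noncentrality (15/30) × √72 = 4.24. Power is 0.987 at alpha 0.05 and 0.941 at 0.01, against the stated 0.986 and 0.943. Reading 30 as the SD at each time point (SD of the difference 42.4) gives 0.841 and 0.638, which does not fit. So 30 is the SD of the paired difference.

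**Step 2: between-week correlation.** 30² = 2 × 30² × (1 − r), so r = 0.5. A correlation w with weekly MVPA is then w/√0.5 with habitual MVPA: 0.28, 0.42 and 0.57.

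**Step 3: expected trait coefficient when the effect is −15 min in every child.** With weekly variance s² = 900 and trait covariance c = 30w, two-predictor least squares gives

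b = c·s²(1 − r)/(s² − c²) = c(1 − r)/(1 − w²).

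- w = 0.2: 6 × 0.5/0.96 = 3.1 min per SD
- w = 0.3: 9 × 0.5/0.91 = 4.9
- w = 0.4: 12 × 0.5/0.84 = 7.1

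**Step 4: how often the 95% interval excludes zero.** Simulation with sex in the model and an identical effect in every child:

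| Setting | w = 0.2 | w = 0.3 | w = 0.4 |
|---|---|---|---|
| One trait, n = 72, r = 0.5 | 17% | 32% | 56% |
| One trait, n = 65, r = 0.5 | 14% | 29% | 52% |
| One trait, n = 72, r = 0.7 | 10% | 20% | 33% |
| Four traits, n = 72, r = 0.5, per trait | 8% | 15% | 28% |
| Four traits, n = 72, r = 0.5, at least one | 27% | 47% | 74% |

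The four-trait rows are closer to the planned model. They assume an inter-trait correlation of about 0.3, and the mean bias falls to about 1.7/3.0/4.6 min per SD.

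**Step 5: the within-child difference as outcome.** Regressing game minus no-games MVPA on sex and trait, without no-games MVPA, gives a mean coefficient of about 0 and about 5% rejection per trait. The chance of at least one of four is about 17–18%, which is ordinary multiplicity.

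**Step 6: if part of the within-child SD is real variation in response.** Suppose half of the 900 is real and unrelated to the trait. Error variance per week is then 225, the covariance of the two weeks is 675, and b = c(1 − 675/900)/(1 − w²) = 1.6/2.5/3.6 min per SD. Single-trait rejection falls to about 7/11/15%.

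**Step 7: if the effect is proportional.** A loss of 15/115 = 13% gives the difference model a slope of its own of about −0.13 × c = −0.8/−1.2/−1.6 min per SD. This is smaller than the bias in Step 3 and opposite in sign.

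**The case against.** The strongest objections concern size and reach, and several stand.

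- The single-trait rates overstate the planned analysis, which enters several traits together. That roughly halves the per-trait figures, although the chance of at least one spurious finding stays well above that of the difference model.
- The value r = 0.5 treats all within-child variation as error. The Background reports that impact differed considerably between pilot children, and Physical activity calls seven days adequate for measuring MVPA. Either point shrinks the bias (Steps 4 and 6).
- The Analysis section does not say that a trait is declared a moderator when its interval excludes zero. That yardstick is used here only to show scale.
- The stated comparison of coefficients between traditional and active games is largely unaffected, because both models carry the same expected bias.
- The aim is exploratory, and the contrasts for hypotheses 1 and 2 are untouched.

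It may also be argued that adjustment and change scores answer different questions and that either is legitimate. That does not hold here. Aim 3 is about a within-child contrast, condition order is randomised and balanced, and the covariate follows the outcome in half the children. The difference estimates that contrast directly at any trait value.

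A reader might infer that every trait tested will appear to modify the effect. The documents do not support that. The bias is in the expected coefficient, significance in one trial is far from certain, and nothing in the article says that attitudes to technology track activity.

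**Conclusion.** The concern holds as a should-fix on an exploratory aim. The model written for hypothesis 3 does not estimate the moderation that the hypothesis describes. For the three traits that the protocol links to activity, its coefficient is biased in the hypothesised direction when the game effect is the same in all children.

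Under the planning figures the bias is about 3.1 to 7.1 min per SD for one trait alone and about 1.7 to 4.6 with four together, against a planned effect of 15 min. This rests on r = 0.5, on trait correlations assumed at 0.2 to 0.4 with weekly MVPA, and on a constant effect in minutes. A more reliable week or real variation in response makes it smaller; neither removes it.

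Similar trait coefficients in the two game models should not be read as replication, because both share the no-games covariate. It would go too far to conclude that the between-game comparison or the primary analysis is compromised.

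**What to change.** In the Analysis section, for each game type, make the dependent variable the within-child difference in MVPA (game condition minus no games). Regress it on sex and the traits, and remove no-games MVPA from the predictors. Equivalently, fit one linear mixed model to the condition weeks with a child random intercept and trait-by-condition terms, and read moderation from those interactions.

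Add a sensitivity analysis on the log ratio of the two weeks. The pilot effects are reported as percentages, and under a proportional effect the difference model has a small slope of its own (Step 7).

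The cost is wording only, with no new data. For a single trait the standard error rises by about 11–13% (roughly 3.6 against 3.25 min per SD at n = 72; 3.6/3.25 = 1.11), and somewhat more with several traits in the model.
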